### Outcomes

Variants of concern (VOC) include:

- B.1.1.7 (Alpha)
- B.1.351, B.1.351.2, B.1.351.3 (Beta)
- B.1.617.2, AY.1, AY.2, AY.3, AY.4, AY.5, AY.6, AY.7, AY.8, AY.9, AY.10, AY.11, AY.12 (Delta)
- P.1, P.1.1, P.1.2 (Gamma)

Variants of interest (VOI) include:

- B.1.525 (Eta)
- B.1.526, B.1.526.1, B.1.526.2 (Iota)
- B.1.617.1 (Kappa)
- B.1.617.3

Other variants

- B.1.427, B.1.429 (Epsilon)
- Any other lineage with 15 or more cases

- Lineage unknown

Groupings and naming of VOC and VOI, except Iota, are determined based on SARS-CoV-2 Variant Classifications and Definitions (2021) by Centers for Disease Control and Prevention (CDC) as of 08/24/2021. (Available from: <https://www.cdc.gov/coronavirus/2019-ncov/variants/variant-info.html>). Sub-lineages B.1.526.1 and B.1.526.2 are added to Iota in addition to B.1.526 considering the phylogenetic finding that the B.1.526 lineage is comprised of these two closely related sub-lineages [16]. Updates may be applied at the time of analysis.

For severe COVID-19 disease, a VOC or VOI with specimen collection date during a hospitalization or with a hospitalization occurring  $\leq 7$  days after the specimen collection date (Day 0 to Day 7) will be identified and chart reviewed. COVID-19 hospitalization is defined as hospitalization with severe COVID-19 disease confirmed by chart review. A VOC or VOI with death during the COVID-19 hospitalization is considered a COVID-19 hospitalized death. These outcomes will only be analyzed if sample sizes are sufficient.

### Exposures

For the 2-dose analysis, the exposure will be defined as receipt of the second dose of Moderna COVID-19 vaccine  $\geq 14$  days prior to the SARS-CoV-2 test date vs. not receiving a dose of any COVID-19 vaccine prior to the SARS-CoV-2 test date.

For the 1-dose analysis, the exposure will be defined as receipt of only 1 dose of Moderna COVID-19 vaccine  $\geq 14$  days prior to the SARS-CoV-2 test date vs. not receiving a dose of any COVID-19 vaccine prior to the SARS-CoV-2 test date.

### Statistical Analysis

Separate analyses will be conducted using the TND for 2-dose and 1-dose VE.

For each VOC or VOI, characteristics of test-positive cases and their matched test-negative controls will be described and compared. Specimens with unsuccessful sequencing may also be considered a test-positive case group for analysis. Continuous covariates such as age in years will be summarized by mean, standard deviation, median, quartiles, minimum, and maximum value, and compared using t-test or Wilcoxon rank-sum test, as appropriate; categorical covariates will be summarized by frequency and percentage and compared using chi-square test or Fisher's exact test, as appropriate. Absolute standardized difference will be calculated to assess the balance of covariates. Potential confounders will be determined based on bivariate analyses and scientific relevance. Given the small sample size and possible need to limit the number of covariates in an adjusted model, potential confounders will be determined by absolute standardized difference (ASD)  $> 0.1$  and  $p\text{-value} < 0.1$ , or scientific relevance.

Conditional logistic regression will be used to estimate the odds ratio (OR) and confidence intervals (CIs) of being vaccinated among cases vs controls, without and with adjustment for potential confounders determined from bivariate analyses. VE (%) will be calculated as  $(1 - \text{OR}) \times 100$ .

The TND analysis will be performed for both an interim analysis and a final analysis. For each interim analysis and final analysis, the test significance level will be adjusted using the Bonferroni correction,  $p = 0.025$  ( $= 0.05/2$  tests). As such, we will be calculating 97.5% CIs for each interim and final analysis. We will provide 95% CIs for each analysis as well. If sample

sizes allow, separate analyses using the same methods described above will be considered for VOCs and VOIs associated with severe COVID-19 disease (COVID-19 hospitalization).

For selected VOCs (e.g., Delta variant), if sample sizes allow, separate analyses will be conducted to assess the VE of Moderna COVID-19 vaccine against SARS-CoV-2 variants by time since most recent Moderna COVID-19 vaccination using the methods similar to those described above. Matching possibly will not be maintained in the subgroup analyses. Matching variables (age, sex, and race/ethnicity) and month of specimen collection will be kept in the adjusted model.

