| Number of patients tested for SARS-CoV-2 with RT-PCR test                       | 48,290      | 825,670 | 184,197 | 1,058,157 |
| Number of patients with a positive SARS-CoV-2 RT-PCR test                       | 13,788      | 200,403 | 24,452  | 238,643   |
| Number of patients with a COVID-19 diagnosis                        | 15,807      | 247,628 | 31,960  | 295,395   |
| Number of patients admitted to hospital with a COVID-19 diagnosis   | 87          | 10,871  | 7,980   | 18,938    |
| Number of patients admitted to ICU with a COVID-19 diagnosis        | 13          | 2,928   | 2,227   | 5,168     |
| Number of deaths within 31 days after the first COVID-19 diagnosis  | 1           | 715     | 2,038   | 2,754     |

A COVID-19 diagnosis includes those with a positive SARS-CoV-2 RT-PCR test result or a COVID-19 diagnosis code only.

As of December 31, 2020, over 1 million SARS-CoV-2 RT-PCR tests had been performed at KPSC, of which 17.4% were among individuals aged ≥65 years and 4.6% were among adolescents aged 12-17 years (Table 2). There were 238,643 members testing positive (13,788 members aged 12-17 years and 24,452 members aged ≥65 years). Additional members were diagnosed with COVID-19 based on positive test results outside of KPSC or clinical presentation and contact history, for a total of 56,752 members with a COVID-19 clinical diagnosis only. Approximately 25.0% (7,980/31,960) of COVID-19 patients aged ≥65 years were hospitalized, compared to only 4.4% (10,871/247,628) who were hospitalized among patients aged 18-64 years and 0.6% (87/15,807) who were hospitalized among patients aged 12-17 years. The proportion of COVID-19 patients being admitted to the ICU was 7.0% in patients aged ≥65 years versus 1.2% in patients aged 18-64 years. The proportion of COVID-19 patients who died within 31 days after a COVID-19 diagnosis or a positive test was 6.4% in patients aged ≥65 years versus 0.29% in patients aged 18-64 years.

As of July 2021, asymptomatic individuals who receive a COVID-19 test at KPSC may include individuals without COVID-19 symptoms who require or request testing. Both vaccinated and unvaccinated individuals are required to be tested for SARS-CoV-2 prior to KPSC procedures or admission. In addition, asymptomatic individuals can request testing (regardless of vaccination status) for any of the following reasons: travel, exposure to or close contact with a COVID-19-

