### 10.1 Test-negative design (TND)

#### Inclusion criteria

- Aged  $\geq 18$  years (aged  $\geq 12$  years once Moderna COVID-19 vaccine is authorized in this age group) as of date of specimen collection for the SARS-CoV-2 test (Day 0)
- KPSC member for  $\geq 12$  months prior to Day 0 (Day -365 to Day 0, inclusive, and allowing a 31-day gap)
- Tested positive for SARS-CoV-2 by PCR at KPSC with specimen collected on or after 3/1/2021 and sent for WGS, without a history of a COVID-19 diagnosis code or SARS-CoV-2 positive molecular test in the 90 days prior to the test; or tested negative for SARS-CoV-2 by PCR with specimen collected on or after 3/1/2021

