### Matching

**Test-positive cases:** Individuals who meet the inclusion/exclusion criteria, and have a positive SARS-CoV-2 test on or after 3/1/2021 with the specimen sent for WGS will be defined as cases. For individuals who have more than one positive test after 3/1/2021, sequencing data from the first specimen will be included in analyses. The date of specimen collection for the positive test will be referred to as the index date.

**Test-negative controls:** Individuals who meet the inclusion/exclusion criteria, have a negative SARS-CoV-2 molecular test on or after 3/1/2021, and do not have a positive test on or after 3/1/2021 will be defined as controls. Controls will be randomly selected and matched, in separate processes, for the 2-dose VE analysis and the 1-dose VE analysis.

Individual matching will be applied for both the 2-dose analysis and 1-dose analysis. Controls will be matched to cases by age group (12-17 years [once Moderna COVID-19 vaccine is authorized in this age group], 18-44 years, 45-64 years, 65-74 years, and 75+ years at specimen collection date), sex, race/ethnicity (Non-Hispanic White, Non-Hispanic Black, Hispanic, Non-Hispanic Asian, and Other/Unknown), and specimen collection date (+/- 10 days). The matched date of specimen collection for the negative test will be the index date for the matched control.

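### The optional severe-disease variant TND compares hospitalized cases with controls tested for any reason in any setting; a second, hospital-route control set would be a cheap improvement

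*Protocol*

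**What the plan says.** All of this is in the Protocol.

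- **Severe analysis (10.1, Statistical Analysis).** Numbers permitting, the text says that "separate analyses using the same methods described above will be considered for VOCs and VOIs associated with severe COVID-19 disease (COVID-19 hospitalization").
- **Severe cases (10.1, Outcomes).** A candidate case is "a VOC or VOI with specimen collection date during a hospitalization or with a hospitalization occurring" within 7 days after the specimen. Candidates "will be identified and chart reviewed", and "COVID-19 hospitalization is defined as hospitalization with severe COVID-19 disease confirmed by chart review". The outcome is analyzed only if numbers suffice.
- **Controls (10.1, Inclusion criteria and Matching).** The criterion for a control's test is "or tested negative for SARS-CoV-2 by PCR with specimen collected on or after 3/1/2021". The rule that makes an eligible person a control reads, in part: "negative SARS-CoV-2 molecular test on or after 3/1/2021, and do not have a positive test on or after 3/1/2021 will be defined". On matching, the plan states that "Controls will be matched to cases by age group", sex, race/ethnicity and specimen date within 10 days. Symptoms, reason for test, setting and admission are not mentioned.
- **Who gets tested (4.2).** "Both vaccinated and unvaccinated individuals are required to be tested for SARS-CoV-2 prior to KPSC procedures or admission". Members without symptoms may also ask for a test for travel, exposure, work, school or any other reason, and KPSC physicians and employees may take weekly saliva tests.
- **Reassurance (Section 10, opening text).** The testing threshold is said not to differ by vaccination status, but this is said only of people with symptoms suggestive of COVID-19.

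**The concern.** In a test-negative design, the vaccination odds among controls stand in for those of the population that would have become cases if infected. That works best when cases and controls reach the test by similar routes. For severe disease the cases reach it largely through illness that leads to admission, where testing is required. Some controls reach it by choosing a test when well. If that choice is related to vaccination, the control odds are shifted and the OR with them.

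The Protocol gives one reason why the two could be related. Healthcare workers were in the first vaccination phase (4.1), and weekly voluntary saliva testing was offered from January 2021 to staff in patient-facing areas (4.2). A person tested weekly has a negative specimen in almost any 10-day-either-way window. Employee status is not a matching factor.

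Variant-specific VE against hospitalization is at stake. The two-dose cohort version of that analysis is itself conditional (Section 10, 10.2), and one-dose variant VE is planned by TND only. For these results the TND may be the only source.

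**Working it through.** **1. The plan's own figure.** Section 10.3 gives 20 cases for a 1:5 matched TND, with 60% of controls vaccinated, VE 0.8 and 80% power. Vaccination among cases at OR 0.2 is 0.2 × 0.6 / (0.4 + 0.2 × 0.6) = 0.12/0.52 = 0.231. At the Bonferroni level of 0.025, taken as two-sided because 97.5% CIs are planned, the unmatched two-proportion formula gives 20 cases. A matched 1:5 formula with no case-control correlation also gives 20 (power 0.816). The figure reproduces and is not in question. What matters is which controls are eligible.

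**2. Cases and controls side by side.**
- Setting: cases are admitted during or within 7 days after the specimen; controls have no condition.
- Reason for test: cases have chart-confirmed severe COVID-19; controls have no condition.
- Shared by matching: age group, sex, race/ethnicity, date.
- Open to adjustment: covariates with ASD above 0.1 and p below 0.1, or of scientific relevance (10.1). Candidates in Table 3 include utilization, prior SARS-CoV-2 testing and employee status. Reason for test and setting are not listed.

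**3. Illustration of size.** Let k be the chance that a vaccinated member supplies a negative elective test, relative to an unvaccinated member. If every control were elective, no case depended on test seeking and nothing were adjusted for:

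observed OR = (1 − VE)/k, so observed VE = 1 − (1 − VE)/k.

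For a true VE of 80%:
- k = 0.8: 1 − 0.2/0.8 = 75%
- k = 1: 80%
- k = 1.25: 1 − 0.2/1.25 = 84%
- k = 1.5: 1 − 0.2/1.5 = 86.7%

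The documents give no value for k; this range is assumed.

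**4. The same point on the 60% coverage of 10.3.** Suppose the population giving rise to severe cases is 60% vaccinated (odds 1.5) and true VE is 80%.
- Controls 50% vaccinated (odds 1.0): observed OR = 0.2 × 1.5/1.0 = 0.30, VE 70%.
- Controls 70% vaccinated (odds 2.333): observed OR = 0.2 × 1.5/2.333 = 0.129, VE 87.1%.

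**5. Mixed controls.** If only a share s of the unvaccinated controls' tests is elective and the rest do not depend on vaccination, k is replaced by (1 − s) + s·k. This lies between 1 and k, so step 3 overstates the shift for a mixed pool.

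**6. Random error at the stated minimum.** With 20 cases (4.6 vaccinated, 15.4 not) and 100 controls (60 and 40), SE of log OR = √(1/4.6 + 1/15.4 + 1/60 + 1/40) ≈ 0.57. An unmatched 97.5% CI is 0.2 × exp(±2.24 × 0.57), or VE from about 28% to 94%.

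**The case against.** The other side has real weight.

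- **The control pool is mixed.** Members testing negative on admission or before a procedure are in it. A reader might infer that most control tests are elective; 4.2 lists reasons for testing but no proportions.
- **The bias need not pass undiluted into the OR.** That would require the assumptions of step 3. Controls are mixed, some severe cases were tested up to 7 days before admission, and the Table 3 proxies can be adjusted for. Greater comorbidity in hospitalized cases is likewise open to adjustment. Adjustment has limits here: 10.1 itself expects that small samples may restrict the number of covariates, and the severe subset is smaller than the full case set.
- **The infection-level TND is no clean benchmark.** A reader might infer that it largely avoids the problem, so that the two VEs cannot be compared. It uses the same any-reason controls, and its cases are not restricted by symptoms or setting. The documents support neither inference.
- **Cancelling care-seeking differences is not the stated reason for the TND.** Section 10 cites use of all sequencing data and easier one- and two-dose analyses. The route-to-test argument is general design reasoning.
- **The analysis is secondary and optional.** At 20 cases its random error exceeds the illustrated shift. This limits the importance of the point, although a larger sample would not remove the bias.
- **Hospital controls are not neutral.** People with severe health conditions had priority for vaccination among those aged 16-64 years (4.1), so hospitalized controls may over-represent the vaccinated.

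What stands is that the text pairs admitted cases with any-reason controls, and nothing planned would show whether that choice affects the result.

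**Conclusion.** This is a cheap improvement to an optional secondary analysis, not an error in a stated figure. As written, the severe-disease variant TND leaves room for bias from any difference by vaccination in elective testing. The reassurance in Section 10 does not cover people without symptoms, and adjustment may reduce the bias without removing it. Neither size nor direction can be derived from the documents. The range of 75% to 86.7% around a true 80% rests on assumed k of 0.8 to 1.5, no adjustment and wholly elective controls, so it shows how the bias works and is not an estimate.

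**What to change.** Add to 10.1 that, if the severe-outcome TND is run, it will also be run with controls whose negative specimen meets the case window: collected during a hospitalization, or with admission on Day 0 to Day 7. Exclude tests taken only for planned procedures and, where the EHR allows, limit to admissions for acute respiratory or COVID-like illness. Keep the other matching variables. Report the results side by side with those from the any-test controls, so that the influence of control choice is visible.

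The cost is a short addition to 10.1 and a second control draw from EHR data already held. There will be fewer controls per case and a second control set to report. The documents do not say whether procedure-only tests can be separated cleanly. Parity would still be incomplete, because cases are chart-confirmed, and selection among hospitalized controls is possible. For these reasons both control sets should be shown, and neither treated as definitive.

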## 10.2 Cohort design

The matched variant cohort will be developed in the same way as the matched cohort assembled for the primary analyses (Section 6.1 and Section 6.2, Study Objectives 1-2), using the same 2-dose Moderna COVID-19 vaccine exposure described in Section 7.1. Because Moderna COVID-19 vaccination began in December 2020 at KPSC, but archiving and WGS of SARS-CoV-2 positive specimens did not begin until March 2021, we will modify the matched cohort from the primary analysis to set index dates to begin no earlier than February 14, 2021 (14 days prior to March 2021). The cohort eligibility criteria will be applied based on the modified index date.

Baseline characteristics of the 2-dose Moderna COVID-19 vaccine cohort will be described and compared between the vaccinated and unvaccinated groups, as for the primary analyses above (Section 8.2). For each VOC or VOI, separately, the incidence of a specific VOC or VOI for the 2-dose vaccinated and unvaccinated individuals will be calculated by dividing the number of individuals with an incident COVID-19 diagnosis with a specific VOC or VOI by the total number of person-years. The person-years for an individual in the cohort will be the time from 14 days after the index date to the date of event of interest, death, disenrollment (allowing for a 31-day gap), end of follow-up (February 28, 2022), or receipt of a dose of any COVID-19 vaccine, whichever comes first. The event date is the date of the first incident COVID-19 diagnosis with a specific VOC or VOI after the index date. In addition, the follow-up time for individuals with an incident COVID-19 diagnosis for which the variant is unknown (i.e., sequencing unsuccessful or not sequenced) or different from the specific variant of interest will be censored on the date of the COVID-19 diagnosis. We will calculate incidence rates of specific VOCs and VOIs, unadjusted and adjusted HRs, and VEs, as described for the primary analyses above (Section 8.3)

If sample size allows, similar analyses will be conducted for VOCs and VOIs associated with COVID-19 hospitalization. Hospitalizations include hospitalized death, but there may be insufficient sample size to assess VE against COVID-19 hospitalized death by variant. Since the cohort analysis will only be conducted at the end of study (February 2022), no adjustment for multiple testing is needed.

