#### 4.3 SARS-CoV-2 Whole Genome Sequencing

KPSC began saving positive molecular SARS-CoV-2 test specimens in March 2021 to conduct whole genome sequencing (WGS). As part of this effort, all positive SARS-CoV-2 molecular test specimens from March 2021 to February 2022 will be sent to an external laboratory for sequencing and variant identification.

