### 7.2 Outcome Definitions

The primary outcomes for this study are:

1. COVID-19 diagnosis will be defined as a SARS-CoV-2 positive molecular test or a COVID-19 diagnosis code (Primary Objective 1, Secondary Objectives 1-12, 14)
2. Severe COVID-19 disease includes COVID-19 hospitalization (hospitalization with a SARS-CoV-2 positive test or a COVID-19 diagnosis, or a hospitalization occurring  $\leq 7$  days after a SARS-CoV-2 positive test, with chart review to confirm severe COVID-19 symptoms) and COVID-19 mortality (death during COVID-19 hospitalization) (Primary Objective 2, Secondary Objectives 13, 15)

We will ascertain the first occurrence of COVID-19 diagnosis or severe COVID-19 disease  $\geq 14$  days after the index date.

Incident COVID-19 cases (identified through diagnosis code or positive molecular test) will be separated into symptomatic and asymptomatic COVID-19 cases. COVID-19 symptoms will be identified using a natural language processing (NLP) algorithm (currently being submitted for publication). The NLP algorithm will be applied to clinical notes before and after the incident COVID-19 diagnosis date to search for COVID-19 related symptoms. COVID-19 cases with no symptoms identified will be considered asymptomatic cases.

Positive SARS-CoV-2 tests conducted for surveillance of asymptomatic individuals will also be used as a preliminary approach to identify asymptomatic COVID-19 cases until the NLP algorithm is finalized. The use of testing data in asymptomatic individuals will facilitate assessment of VE against asymptomatic COVID-19 for the first interim analysis, whereas the

more comprehensive NLP approach will require more time to apply and will be used for subsequent analyses.

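### The cohort variant analysis censors diagnoses of unknown variant as if they were another variant, so the variant-specific incidence rates are too low by the untyped share

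*Protocol*

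**What the plan says.** Protocol Section 10.2 names variant-specific incidence rates as an output, alongside HRs and VEs. The rate comes from "dividing the number of individuals with an incident COVID-19 diagnosis with a specific VOC or VOI by the total number of person-years". For all other cases the rule reads: "for which the variant is unknown (i.e., sequencing unsuccessful or not sequenced) or different from the specific variant of interest will be censored". Follow-up therefore stops at the diagnosis.

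Two other sections determine who can be typed. Section 7.2 sets the outcome: "COVID-19 diagnosis will be defined as a SARS-CoV-2 positive molecular test or a COVID-19 diagnosis code". Section 4.3 sets the sequencing input: "all positive SARS-CoV-2 molecular test specimens from March 2021 to February 2022 will be sent to an external laboratory". Section 4.2 explains that, beyond those who tested positive, further members were diagnosed from outside tests or from clinical presentation and contact history, "for a total of 56,752 members with a COVID-19 clinical diagnosis only".

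Section 10 allows the cohort analysis only at the final analysis, and only if two proportions among COVID-19 cases are similar between arms: positive tests at KPSC, and positive specimens sent for sequencing. Section 13 notes that sequencing may fail at low viral load, and that this may be more common in vaccinated people.

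**The concern.** Censoring is right for a diagnosis known to be a different variant, because that is a competing event. A diagnosis of unknown variant is different: some of these diagnoses are the variant being counted. Section 10.2 gives both the same treatment, so an untyped diagnosis is an event for no variant. The numerator holds only successfully typed cases, while the denominator holds everyone's person-time up to any diagnosis.

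Code-only diagnoses enter the outcome but can never be typed, so some shortfall is built in even if every specimen sequences successfully. The condition in Section 10 compares the arms and sets no minimum level. Two arms with the same large untyped share would pass it and still report rates that are too low.

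A second consequence concerns VE. The condition looks at specimens sent, not specimens successfully sequenced. If sequencing fails more often in vaccinated people, censoring removes proportionally more vaccinated events and VE rises.

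**Working it through.** **Inputs.** Section 4.2 and Table 2 (calendar 2020) give members with a positive KPSC RT-PCR test and members with any COVID-19 diagnosis, by age. The protocol gives no sequencing failure rate, so the values used below are assumptions.

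**Reproducing the plan's figure.** 295,395 − 238,643 = 56,752, which matches Section 4.2 exactly.

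**Share with no KPSC specimen** = (diagnoses − positives) / diagnoses:

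| Age | Diagnoses | KPSC positive | Difference | Share |
|---|---|---|---|---|
| 12-17 | 15,807 | 13,788 | 2,019 | 12.8% |
| 18-64 | 247,628 | 200,403 | 47,225 | 19.1% |
| ≥65 | 31,960 | 24,452 | 7,508 | 23.5% |
| Total | 295,395 | 238,643 | 56,752 | 19.2% |

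**Effect on the rate.** Let p be the probability that a diagnosis is typed, taken as unrelated to which variant it is. Follow-up ends at any diagnosis, typed or not, so person-time does not depend on p. Hence reported rate = p × true variant rate, and the shortfall is 1 − p.

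- 2020 share, perfect sequencing: p = 238,643/295,395 = 0.808; shortfall 19.2%.
- With an assumed 10% failure: p = 0.808 × 0.90 = 0.727; shortfall 27%.
- With an assumed 20% failure: p = 0.808 × 0.80 = 0.646; shortfall 35%.
- If every diagnosis had a KPSC specimen, the shortfall would be the failure rate alone: 10% or 20%.

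**Effect on HR and VE when typing is equal.** Take illustrative true rates of 0.0540 (unvaccinated) and 0.0108 (vaccinated) per person-year, so VE = 0.80. Multiplying both by 0.808 gives 0.0436 and 0.0087, and VE = 1 − 0.0087/0.0436 = 0.80. The factor p cancels. A simulation with 2,000,000 people per arm gave VE 0.801 both for typed cases only and for all cases of the variant.

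**Effect when sequencing success differs.** Reported HR = true HR × (success in vaccinated / success in unvaccinated). With assumed success of 75% and 90%, the ratio is 0.833.

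- True VE 80%: HR 0.20 × 0.833 = 0.167, so reported VE is 83%.
- True VE 50%: HR 0.50 × 0.833 = 0.417, so reported VE is 58%.

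**The case against.** The strongest reply is that Objective 16 asks for VE, and with equal typing VE does not move. The analysis is secondary and conditional. Section 10.2 says openly what is counted and censored, Section 10 plans to describe the percentage of specimens with valid sequencing by vaccination status, and Section 13 lists sequencing failure as a limitation. This stands as a limit on importance. It does not make the rates correct: they are a named output, and no step rescales them or marks them as typed-only. The planned description covers specimens, so it leaves out code-only diagnoses, and it is not tied to the decision to run the analysis.

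A reader might infer that the rates are at least a fifth too low in both arms. The documents do not support such a floor. The 19.2% is a 2020 figure, before the March 2021 to February 2022 sequencing window, during which testing was still expanding, and it is not split by vaccination status. It is 12.8% at ages 12-17. Some diagnoses made on clinical presentation and contact history may not be infections, and leaving those out is no undercount.

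A reader might also infer harm to rate differences, cases averted or the sum of variant rates. The protocol plans no rate difference or cases-averted figure. Nor does it promise that variant rates add up to the overall rate; the variant cohort has its own index dates and end of follow-up.

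Finally, replacing the main HR with a weighted one would be debatable. Arm by 12 months by 5 age groups is 2 × 12 × 5 = 120 cells, while Section 10.3 contemplates about 15 unvaccinated cases of a variant. That objection stands, and the fix respects it.

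**Conclusion.** The point holds for the incidence rates. Each arm's variant-specific rate is too low by that arm's untyped share. The size is about 19% if the 2020 code-only share persists into the sequencing window and those diagnoses are true infections. It is 27% or 35% if, in addition, 10% or 20% of specimens fail sequencing. If nearly all diagnoses in the window have a KPSC specimen, it falls to the sequencing failure rate.

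It does not follow that the planned VE is biased: with equal typing in both arms, HR and VE are unaffected. VE is biased upward only if sequencing fails more often in vaccinated people. Section 13 raises that possibility without giving a rate, and the condition in Section 10 would not detect it. The change should be made, but it concerns a conditional secondary analysis and does not touch the primary objectives.

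**What to change.** In Section 10.2:

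- Keep censoring for diagnoses typed as another variant.
- For the variant incidence rates, treat untyped diagnoses as events of missing type. Use inverse-probability-of-typing weights or multiple imputation within arm and coarse calendar-period and age cells, adding Ct value where a specimen exists. Show results with and without code-only diagnoses, since some of these may not be infections.
- Keep the planned typed-only Cox HR as the main VE result, and give the weighted or imputed HR as a sensitivity analysis.
- Report the number and rate of untyped diagnoses by arm, split into code-only and failed sequencing, and label any unweighted rates as typed-only.

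In Section 10, add the proportion successfully sequenced to the proportions that must be similar between arms before the cohort analysis is run.

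The cost is a short addition to the text and modest extra programming. The statistical price is the assumption that type is missing at random within the cells. That is weakest for code-only diagnoses, which have no Ct value.
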